### Neurological status immediately before procedure

Unconsciousness before sedation, hemiplegia/hemiparesis, paraplegia/paraparesis, dysarthria/aphasia, vision loss, confusion, or intubated/sedated at arrival. These conditions will be reported as separate variables.

### Malperfusion

Malperfusion refers to acute organ ischemia secondary to aortic branch vessel hypoperfusion. This severe condition is usually classified based on clinical signs and symptoms [15, 16]. Herein, myocardial malperfusion will be defined as any changes in ST level in electrocardiogram and/or an increase in cardiac enzymes. Cerebral malperfusion will be defined as acute preoperative stroke. Spinal malperfusion will be defined as acute paraparesis/paraplegia. Mesenteric malperfusion will be as sudden, mild-to-severe abdominal pain with or without nausea and vomiting, which is accompanied or not by rectal bleeding or bloody diarrhea [17]. Renal malperfusion will be defined as anuria/oliguria. Peripheral malperfusion will be defined as loss of pulse with or without sensory or motor deficits of any limb.

### Preoperative computed tomography findings

Preoperative computed tomography scans will be reviewed for evaluation of the extent of aortic dissection/intramural hematoma in different segments of the aorta and its branches. Dissection of the aortic branches will be defined as any intimal flap at the origin of the artery causing stenosis of any severity. This applies also to aortic branches perfused through the false lumen.

Data on maximal diameter of the aortic root, ascending aorta, aortic arch, descending aorta and abdominal aorta will be collected.

### Intramural hematoma

A contained aortic wall hematoma within the media, but without intimal flap formation of the ascending aorta. Patients will be considered as having aortic intramural hematoma when no concomitant aortic intimal flap was observed at preoperative aortic imaging. When intramural hematoma was associated with an intimal flap of any other segment of the aorta, this will be classified as a true aortic dissection.

### Heart valve status and left ventricular function

Data from preoperative echocardiographic evaluation of the aortic valve, mitral valve and left ventricular function will be collected.

### Arterial and venous cannulation sites

It refers to the primary cannulation sites. Any switch to other cannulation site before initiation of cardioplegia will be described.

### Intraoperative findings

Data on the intraoperative findings of the pericardium, ascending aorta and aortic arch will be collected. The extent of aortic dissection at the level of the Valsalva sinuses and morphology of the aortic valve will be described.

### Surgical repair

Data on the type of aortic root/ascending aorta and aortic arch surgical repair will be collected along with data on any concomitant major cardiac surgery procedure. Details regarding the level of aortic anastomosis will be documented. In particular, data on aortic anastomosis suture techniques (i.e. the use and number of layers of Teflon or pericardial patch to reinforce the anastomosis and the aortic wall) and the use of biological glue to the dissected tissues will be retrieved. Double layer reinforcement patch technique refers to an anastomosis suture with a combination of one patch outside the aorta and the other between the dissected tissues or from inside the aorta. Triple layer reinforcement patch technique refers to an anastomosis suture with a combination of one patch outside the aorta, one within the dissected tissues and one from inside the aorta.

### Cardiopulmonary bypass parameters

Data on duration of myocardial ischemia, cardiopulmonary bypass, hypothermic circulatory arrest and retrograde or antegrade cerebral perfusion will be collected. When multiple periods of perfusion or organ ischemia have occurred, the total length of these periods will be reported. The lowest temperature during hypothermic circulatory arrest will be documented.

## Outcomes and their definition criteria

### Hospital death

All-cause death having occurred during the index hospitalization, i.e. at the institution where surgery for TAAD was performed.

### Acute heart failure

Postoperative heart failure requiring prolonged use of inotropes (> 24 h) and/or the insertion of any mechanical circulatory support device.

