**Methods:**

Nineteen centers of cardiac surgery from seven European countries have collaborated to create a multicentre observational registry (ERTAAD), which will enroll consecutive patients who underwent surgery for acute TAAD from January 2005 to March 2021. Analysis of the impact of patient’s comorbidities, conditions at referral, surgical strategies and perioperative treatment on the early and late adverse events will be performed. The investigators have developed a classification of the urgency of the procedure based on the severity of preoperative hemodynamic conditions and malperfusion secondary to acute TAAD. The primary clinical outcomes will be in-hospital mortality, late mortality and reoperations on the aorta. Secondary outcomes will be stroke, acute kidney injury, surgical site infection, reoperation for bleeding, blood transfusion and length of stay in the intensive care unit.

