### Stroke

Acute episode of a focal or global neurological deficit with at least one of the following: change in the level of consciousness, hemiplegia, hemiparesis, numbness, or sensory loss affecting one side of the body, dysphasia or aphasia, hemianopia, amaurosis fugax, or other neurological signs or symptoms consistent with stroke duration of a focal or global neurological deficit ≥24 h; OR < 24 h if available neuroimaging documents a new brain hemorrhage or infarct; OR the neurological deficit results in death [18]. Stroke will be classified as ischemic, hemorrhagic or both.

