### Acute kidney injury

It will be defined according to postoperative change in serum creatinine levels and its severity will be stratified according to the Kidney Disease: Improving Global Outcomes (KDIGO) criteria [19] (Table 5). However, in view of the prolonged hospital treatment of TAAD patients, changes in serum creatinine level will be evaluated as occurring during the entire index hospitalization. We recognize that acute kidney injury can also be diagnosed according to urine output measure. However, this method is not feasible in retrospectively gathered data and therefore it will not be considered in the present study. Dialysis will be defined as temporary when discontinued and permanent if continued at the time of discharge from the institution where surgery for acute TAAD was performed.

**Table 5 Tab5:** Definition criteria of postoperative acute kidney injury.^a^

Stages	Serum creatinine
1	1.5–1.9 times baseline OR ≥0.3 mg/dL (≥26.5 micromol/L) increase
2	2–2.9 times baseline
3	≥3.0 times baseline OR Increase to ≥4 mg/dL (≥353.6 micromol/L) OR Initiation of renal replacement therapy

^a^Changes in serum creatinine level occurring during the index hospitalization

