### Mechanical circulatory support

The use of intra-aortic balloon pump and/or venoarterial extracorporeal membrane oxygenation for postoperative acute heart failure. The duration of treatment of these salvage therapies will be documented.

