Logistic and linear regression analyses will be employed to identify independent risk factors for early adverse events with and without a stepwise approach. For the purpose of developing a risk scoring method from this registry, the study cohort will be randomly divided into two datasets, i.e. the derivation data set (75.0% of patients) and the validation data set (25.0% of patients). Univariate analysis will be performed on all candidate covariates of the derivation dataset to identify predictors of in-hospital mortality. Multiple logistic regression analysis will be then performed using the derivation dataset. A stepwise procedure with a bootstrap approach will be used, and 100 samples will be extracted with a size of 70% of the derivation dataset. A stepwise procedure will be applied to each sample (probability to stay = 0.05; probability to entry = 0.1). Variables selected in at least 50% of the stepwise procedures will be included in the regression model. Additional covariates were selected using a forward selection comparing the Akaike information criterion for the models with and without each covariate. The model with the lowest Akaike information criterion will be selected for each forward step, until the inclusion of a new covariate determined an increase in the Akaike information criterion value. The model will be tested in the validation data set for calibration, using the Hosmer–Lemeshow test, and for discrimination using the receiver-operating characteristic curve analysis. A comparison of the predictive ability of the new score with the current risk scoring methods for prediction of in-hospital mortality will be performed in the overall dataset as well as in the validation dataset using the DeLong test. The improvement of discrimination of the new score will be estimated by calculating the net reclassification index and the integrated discrimination improvement. Finally, to evaluate the adaptability of the new score for prediction of late mortality, Kaplan–Meier curves stratified by deciles of the new score will be plotted.

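### The acute heart failure definition has no clause for early death: a patient who dies within 24 h on inotropes, without a mechanical support device, is scored as having no heart failure

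*Protocol article*

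**What the plan says.** Under Outcomes and their definition criteria, the protocol article defines acute heart failure as "Postoperative heart failure requiring prolonged use of inotropes (> 24 h) and/or the insertion of any mechanical circulatory support device". There are two routes to the event: inotropes for more than 24 h, or a device. The entry on mechanical circulatory support describes the devices as "The use of intra-aortic balloon pump and/or venoarterial extracorporeal membrane oxygenation for postoperative acute heart failure" and sets no minimum duration. Neither entry says how a patient who dies before 24 h is classified, and no other section does.

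The stroke definition, which follows directly, also uses a 24 h duration. It adds two exceptions: a shorter deficit with positive imaging, and "OR the neurological deficit results in death".

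Hospital death is a separate outcome: "All-cause death having occurred during the index hospitalization". For the analysis, the Statistical analysis section says "Logistic and linear regression analyses will be employed to identify independent risk factors for early adverse events". It reserves competing-risk methods for late non-fatal events.

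**The concern.** A duration threshold on a treatment can be met only by a patient who lives long enough to reach it. Read literally, a patient in low output who dies at 10 h on inotropes without a device has no acute heart failure, while a patient weaned at 26 h who goes home has it. The more severe case is scored as the better one.

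Such errors are unlikely to be spread evenly. The registry sets out to study preoperative condition, urgency and surgical strategy. Its salvage grade 1 category includes patients who deteriorate after induction because of acute heart failure, tamponade or rupture. Very early low-output deaths plausibly cluster in groups of that kind. If they do, a model of acute heart failure would understate the effect of the factors that lead to its fatal form.

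**Working it through.** The plan states no rate, event count or power for acute heart failure, so there is no figure to reproduce. The check is one of logic, followed by an illustrative range.

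**1. Cases for a patient with postoperative heart failure on inotropes**

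| Course | Inotropes > 24 h | Device | Scored as |
|---|---|---|---|
| Weaned at 26 h, survives | yes | no | event |
| Dies within 24 h, device inserted | no | yes | event |
| Dies within 24 h, no device | no | no | **no event** |

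Only the third row is misclassified. In the second row the device route applies, because it has no minimum duration.

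**2. Comparison with stroke**

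Both definitions contain a 24 h duration. For stroke, death from the deficit replaces the duration. For heart failure, nothing does. The same course (onset, then death from the condition before 24 h) is an event under one definition and a non-event under the other.

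**3. Effect on a comparison**

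For groups 1 and 0, let p be the true event rate and m the fraction of patients in the third row. The recorded rate is p − m, so:

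recorded difference = (p1 − p0) − (m1 − m0)

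If m is the same in both groups, the risk difference is unchanged. If the group with more heart failure also has more early deaths without a device (m1 > m0), the recorded difference is too small. The documents give neither m1 nor m0.

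**4. Illustrative size**

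Inputs from the protocol article: more than 6000 patients expected (Sample size calculation), taken as 6000; 30-day mortality of 17% (Background, where the other cited figures are 16.9% and 18%).

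- Early deaths: 6000 × 0.17 = 1020.
- Assumption: 5% to 20% of these fall in the third row.
- Misclassified: 1020 × 0.05 = 51, to 1020 × 0.20 = 204.
- Share of the cohort: 51/6000 = 0.9%, to 204/6000 = 3.4%.

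A second set of assumptions is that 20% to 40% of early deaths occur within 24 h and that 40% to 60% of those are low-output deaths without a device. This gives 0.17 × 0.2 × 0.4 = 1.4%, to 0.17 × 0.4 × 0.6 = 4.1%. The two ranges overlap, but only the 17% comes from the document.

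**The case against.** The strongest reply is that little depends on this definition. The abstract states "The primary clinical outcomes will be in-hospital mortality, late mortality and reoperations on the aorta", and then "Secondary outcomes will be stroke, acute kidney injury, surgical site infection, reoperation for bleeding, blood transfusion" and length of intensive care stay. Acute heart failure is in neither list. The Statistical analysis section names no heart failure model, and the risk score it describes predicts in-hospital mortality. A patient in the third row who dies in the operating hospital is counted under hospital death, so an excess of early cardiac deaths would show in a primary outcome. This stands, and it limits the consequence. It does not repair the definition: acute heart failure is a defined registry outcome, models of early adverse events are planned, and counting the death elsewhere does not correct a heart failure model.

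A second reply is that a death clause brings in judgement. The registry collects all-cause death, and no section asks for cause of death. Tamponade, rupture and malperfusion are competing explanations for a very early death, and 19 centers could attribute deaths differently. This also stands. It argues for a clause tied to a recordable fact, such as being on inotropes at the time of death, rather than to a cause of death.

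A third reply is that an analysis plan not shown may handle early death. It may do so in the analysis, but the rule that decides who has the event is fixed in this article and is applied when records are abstracted.

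**Conclusion.** The gap is real and narrow. Patients with postoperative heart failure who die within 24 h on inotropes and without a device are scored as having no acute heart failure, although the neighbouring stroke definition covers the same situation. This can bias logistic models of this one outcome. The documents do not give the size; 0.9% to 3.4% of the cohort rests on the assumed 5% to 20% share of early deaths.

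Four stronger readings are not supported:

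- A reader might infer that every early death on inotropes is missed. Those with a device are counted.
- A reader might infer that a strategy's early cardiac harm would disappear from the registry. Death in the operating hospital is a primary outcome.
- A reader might infer a known bias towards no effect. The direction depends on how these deaths are distributed between groups, which the documents do not show.
- A reader might infer that the dialysis rule ("Dialysis will be defined as temporary when discontinued and permanent if continued at the time of discharge") shares the flaw and puts the worst renal outcomes in a milder class. Table 5 places any start of renal replacement therapy in stage 3, and the article does not say that death on dialysis is coded as discontinuation.

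**What to change.** Extend the inotrope criterion so that acute heart failure is met by inotropes for more than 24 h, or by being still on inotropes for postoperative heart failure at death within 24 h of surgery, with the device route kept as it is. This follows the logic of the stroke definition without requiring a cause of death.

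Add a sensitivity analysis for this outcome that handles death within 24 h without the event in one of two ways: as part of a composite with acute heart failure, or as a competing event. This shows whether conclusions depend on how the earliest deaths are classified.

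The cost is one line in the definition, a check of inotrope use in the records of patients who died within 24 h, and one extra analysis. The downside is some abstractor judgement on whether heart failure was present in very early deaths; the sensitivity analysis shows how much that matters. The change affects data classification only, not patient care.

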### Stroke

Acute episode of a focal or global neurological deficit with at least one of the following: change in the level of consciousness, hemiplegia, hemiparesis, numbness, or sensory loss affecting one side of the body, dysphasia or aphasia, hemianopia, amaurosis fugax, or other neurological signs or symptoms consistent with stroke duration of a focal or global neurological deficit ≥24 h; OR < 24 h if available neuroimaging documents a new brain hemorrhage or infarct; OR the neurological deficit results in death [18]. Stroke will be classified as ischemic, hemorrhagic or both.

### Global brain ischemia

Diffuse hypoxic damage as diagnosed at brain imaging and electroencephalography.

### Paraplegia/paraparesis

Bilateral weakness and/or multimodality sensory disturbance below the level of the ischemic spinal lesion.

### Mesenteric ischemia

Abdominal pain with or without nausea and vomiting and rectal bleeding or bloody diarrhea [17]. Diagnosis is done at imaging, endoscopy and/or surgery.

### Acute kidney injury

It will be defined according to postoperative change in serum creatinine levels and its severity will be stratified according to the Kidney Disease: Improving Global Outcomes (KDIGO) criteria [19] (Table 5). However, in view of the prolonged hospital treatment of TAAD patients, changes in serum creatinine level will be evaluated as occurring during the entire index hospitalization. We recognize that acute kidney injury can also be diagnosed according to urine output measure. However, this method is not feasible in retrospectively gathered data and therefore it will not be considered in the present study. Dialysis will be defined as temporary when discontinued and permanent if continued at the time of discharge from the institution where surgery for acute TAAD was performed.

**Table 5 Tab5:** Definition criteria of postoperative acute kidney injury.^a^

Stages	Serum creatinine
1	1.5–1.9 times baseline OR ≥0.3 mg/dL (≥26.5 micromol/L) increase
2	2–2.9 times baseline
3	≥3.0 times baseline OR Increase to ≥4 mg/dL (≥353.6 micromol/L) OR Initiation of renal replacement therapy

^a^Changes in serum creatinine level occurring during the index hospitalization

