### Baseline and postoperative laboratory parameters

Baseline levels of hemoglobin, creatinine, platelets, arterial lactate, cardiac enzymes and C-reactive protein as well as postoperative lowest levels of hemoglobin and platelets and postoperative peak levels of creatinine and arterial lactate will be collected.

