### Renal function

Renal function will be classified according to the estimated glomerular filtration rate (eGFR) calculated using the Chronic Kidney Disease Epidemiology Collaboration (CKD-EPI) equation [9] and the European Kidney Function Consortium (EKFC) equation [10]. The severity of renal failure will be classified in different stages as listed in Table 2.

**Table 2 Tab2:** Stages of chronic kidney disease

Stages	eGFR (mL/min/1.73 m^**2**^)
1	≥90
2	60–89
3a	45–59
3b	30–44
4	15–29
5	< 15 or dialysis

*eGFR* estimated glomerular filtration rate

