### Critical preoperative state

Ventricular tachycardia or ventricular fibrillation or aborted sudden death, preoperative cardiac massage, preoperative ventilation before anesthetic room, preoperative inotropes, preoperative acute renal failure (anuria or oliguria < 10 ml/hr) [12]. These conditions will be reported as separate variables.

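### The acute kidney injury and dialysis outcomes set no condition for patients already on dialysis, and the stand-alone 4 mg/dL limb can score a trivial creatinine rise as stage 3

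*Protocol article*

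**What the plan says.** The section on acute kidney injury says of the outcome: "It will be defined according to postoperative change in serum creatinine levels". Severity is graded by Table 5 over the whole index hospitalization, and urine output is not used. Stage 1 is "1.5–1.9 times baseline OR ≥0.3 mg/dL (≥26.5 micromol/L) increase". Stage 3 is "≥3.0 times baseline OR Increase to ≥4 mg/dL (≥353.6 micromol/L) OR Initiation of renal replacement therapy".

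The same section calls dialysis temporary when it was discontinued and "permanent if continued at the time of discharge from the institution where surgery for acute TAAD was performed".

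On who is in the cohort:

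- Table 2 (Renal function) has a stage 5 defined as "< 15 or dialysis", so the registry expects patients on dialysis before surgery.
- The section on critical preoperative state records "preoperative acute renal failure (anuria or oliguria < 10 ml/hr" as a separate baseline variable.
- The exclusion criteria cover age, symptom onset, prior procedure, retrograde dissection, endocarditis and trauma. None is renal.

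The laboratory section collects "Baseline levels of hemoglobin, creatinine, platelets, arterial lactate, cardiac enzymes and C-reactive protein" and "postoperative peak levels of creatinine and arterial lactate will be collected". It gives no time point for the baseline value.

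**The concern.** A postoperative complication should be counted among patients who can still develop it. A patient on chronic dialysis cannot newly become dialysis-dependent, and a small change in that patient's creatinine says little about the operation. The section on acute kidney injury sets no at-risk condition, so two kinds of pre-existing disease can enter the outcome:

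- advanced kidney disease with a trivial rise, through the 4 mg/dL limb of stage 3;
- chronic dialysis, through the label for dialysis ongoing at discharge.

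AKI is a named secondary outcome in the abstract. Early adverse events feed the risk-factor models and the comparisons between centres and surgeons in the statistical analysis section. Such misclassification would follow baseline renal disease, and the registry sets out to study how preoperative condition relates to outcome.

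**Working it through.** The article gives no figure to reproduce here. The check applies Table 5 literally to example patients and then sizes the dialysis label under stated assumptions.

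**Step 1. Table 5 applied literally.** The rules, with peak compared with baseline, are:

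- stage 3 if the ratio is at least 3, or creatinine increases to 4 mg/dL or more, or renal replacement is initiated;
- stage 2 if the ratio is at least 2;
- stage 1 if the ratio is at least 1.5 or the rise is at least 0.3 mg/dL.

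The units in Table 5 agree with each other: 0.3 × 88.4 = 26.52 and 4 × 88.4 = 353.6 micromol/L. The creatinine values below are illustrative and not from the article.

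| Patient | Baseline to peak (mg/dL) | Ratio | Rise | Meets a stage 1 threshold? | Table 5 result |
|---|---|---|---|---|---|
| Advanced kidney disease | 3.9 to 4.0 | 1.03 | 0.1 | No | Stage 3 |
| Advanced kidney disease | 3.8 to 4.0 | 1.05 | 0.2 | No | Stage 3 |
| Chronic dialysis | 6.0 to 6.2 | 1.03 | 0.2 | No | Stage 3 |
| Chronic dialysis | 6.0 to 7.0 | 1.17 | 1.0 | Yes (rise) | Stage 3 |
| Chronic dialysis | 6.0 to 5.5 | 0.92 | −0.5 | No | No AKI |

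The first three rows reach the top grade without qualifying for the lowest. The fourth shows that tying the 4 mg/dL limb to a stage 1 rise would not remove every dialysis patient, so an at-risk condition is needed as well. The last shows that pre-existing renal failure is not always scored as an event. In none of the dialysis rows does the renal replacement limb apply, because treatment was continued and not initiated.

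**Step 2. The dialysis label.** The definition looks only at whether dialysis had stopped or was continuing at discharge. A chronic dialysis patient who reaches discharge on dialysis meets the wording for permanent dialysis.

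Let p_pre be the share on dialysis before surgery and p_new the rate of new dialysis among the rest. If every preoperative dialysis patient is counted as having dialysis:

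recorded rate = p_pre + (1 − p_pre) × p_new

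The article gives neither input. The ranges assumed are p_pre 1–2% (60–120 of 6000 patients) and p_new 8–12%.

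| p_pre | p_new | Recorded rate | Relative inflation |
|---|---|---|---|
| 1% | 8% | 0.01 + 0.99 × 0.08 = 8.92% | 8.92/8 − 1 = 11.5% |
| 2% | 8% | 0.02 + 0.98 × 0.08 = 9.84% | 9.84/8 − 1 = 23.0% |
| 1% | 12% | 0.01 + 0.99 × 0.12 = 12.88% | 12.88/12 − 1 = 7.3% |
| 2% | 12% | 0.02 + 0.98 × 0.12 = 13.76% | 13.76/12 − 1 = 14.7% |

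This sizes the dialysis rate only. No effect on AKI incidence can be computed, because the article gives no distribution of baseline creatinine.

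**The case against.** **The eligibility criteria define the registry, not the AKI denominator.** Leaving prior-dialysis patients out of one secondary outcome could be settled in a fuller document that is not shown. That is fair as to intent. But the article states this outcome definition in detail, including its own departures from the KDIGO criteria (the longer window, no urine output). As stated, it yields the results above.

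**The text separates defining AKI by a change in creatinine from grading its severity.** On that reading, 3.9 to 4.0 mg/dL need not be a case at all. The reading is possible, but Table 5 is itself presented as the criteria that define postoperative AKI, and the text sets no minimum change outside it.

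**Planned adjustment will deal with case mix.** The propensity model takes in all available baseline variables, and centre rates are risk-adjusted. This reduces the imbalance between groups but does not correct a mislabelled outcome.

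**Two stronger readings are not supported.** A reader might infer that continued chronic dialysis is stage 3 by the renal replacement limb; the word initiation rules that out. A reader might also infer that baseline is fixed as the acute admission value, so that renal malperfusion is scored as no AKI. The article never fixes the time point. Listing baseline creatinine beside arterial lactate and cardiac enzymes makes an admission value likely, but no more.

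Even if baseline is the admission value, the consequence is limited. From 2.0 mg/dL on admission, a peak of 2.2 is no AKI (ratio 1.1, rise 0.2), but a peak of 2.3 is stage 1 and starting dialysis is stage 3. Patients with a raised admission creatinine are therefore not all missed. Measuring further deterioration from the preoperative state is also defensible for an outcome labelled postoperative.

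**Conclusion.** The point holds as a defect in the wording of the acute kidney injury section and Table 5. Patients on dialysis before surgery are not removed from either outcome, ongoing dialysis at discharge need not be new, and the 4 mg/dL limb requires no minimum rise. These three statements rest on the text alone.

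The size is not known from the documents. The 7–23% relative inflation depends on the assumed 1–2% and 8–12% and on counting every preoperative dialysis patient. It concerns the dialysis rate and not the named AKI outcome. The affected subgroup is probably small, AKI is a secondary outcome, and no stated sample size depends on it. The change is worth making because it is cheap and the outcome is used to compare strategies and centres. That baseline creatinine has no time point is a separate gap, to be closed by one sentence; it does not show that malperfused patients are misclassified.

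**What to change.** In the section on acute kidney injury:

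1. Exclude patients on dialysis before surgery from the denominators of the AKI and postoperative-dialysis outcomes, and report their number.
2. Count only newly started dialysis, and rename the permanent category as new dialysis ongoing at discharge from the operating centre.
3. Apply the 4 mg/dL criterion only when the rise is also at least 0.3 mg/dL or at least 1.5-fold.
4. State that baseline creatinine is the last preoperative value, if that is what is collected.
5. Keep patients with preoperative acute renal failure or renal malperfusion in the main analysis, and add a sensitivity analysis without them. Both conditions are defined by urine output, so a patient with raised creatinine but preserved urine output would stay in; the report should say so.

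The cost is wording, a filter on baseline renal data and one sensitivity analysis. Table 2 merges dialysis with eGFR below 15, so the filter needs preoperative dialysis to be identifiable on its own in the datasheet. The AKI denominator becomes slightly smaller.
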